### Procedure

Inclusion commenced in September 2018, but inclusion is recently stopped due to Covid-19. Data collection is still ongoing. Participants are being recruited from one academic hospital in the Netherlands where they received their kidney transplant or from the local hospital after referral for post-transplant care. Patients who are eligible for the study are informed about the study by the healthcare professional at the end of their regular appointment. Thereafter the healthcare professional or someone from the research team hands out written information on the study (PIF). The healthcare professional was provided with a standardized script on introducing the study. After having time to consider participation, the researcher contacts the patients by telephone to provide additional information (when needed), answer questions, ask for consent and make an appointment to obtain written consent. This appointment can take place at the patient’s home and the important other is also invited to attend. After written consent from both parties is obtained, the first questionnaires are completed (T0) and the electronic monitoring device is explained and handed out. Since evidence suggests that adherence will be statistically higher when patients start to use the electronic monitoring device [38], a run-in period of 35 days (+/− 7 days) is incorporated. A second appointment is made to coincide with the end of the run-in period (T1), during which a second set of questionnaires is completed by patient and important other, and EM data is collected. Group assignment is revealed after questionnaires have been completed. For the following 6 months patients allocated to the experimental group receive the intervention and the control group receives CAU. Six months after T1 participants are asked to complete questionnaires and EM data is collected (T2). Subsequently, patients continue using the EM device for the follow-up period of 6 months and questionnaires are also completed at the end of this 6 months (T3) (see Fig. 1 for flow-diagram) .

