### Effect evaluation

#### Primary outcome measure

The primary endpoint of this study is medication adherence registered with EM, since this is referred to as the gold standard [31, 32]. A commonly used device to monitor adherence is the Medication Event Monitoring System (MEMS) bottle caps. However, the MEMS-caps have a few disadvantages such as the need to diverge from the regular Dosette box which may be confusing for patients because they have to use multiple boxes for their medications and they cannot check if they took their medication [46]. Therefore, we are using another innovative device for electronic monitoring, called the Silent Card (Adherence Innovations, Nijmegen). This silent card is being validated and negates the shortcomings of the MEMS-caps. The silent card is less invasive and disruptive for the patient since it can be used in combination with the regular Dosette box. The device can be fixed to the Dosette box and every time the immunosuppressive medication is taken, the patient needs to push a button on the card. Patients who prefer other ways of storing their medication can also use the silent card without making any alterations to their medication regimen, they simply keep the card with their medication and press the button to indicate having taken the medication. A chip registers the dates and times the button on the silent card is pressed. Data is extracted from the Silent Card using an tablet containing Near Field Communication (NFC) and Bluetooth to connect the Silent Card to the SilentReminderE app, specially developed for the Silent Card. This data is then transferred to the computer.

Medication adherence is operationalized as being adherent ≥95% as registered by the EM. We apply this stringent cut-off, as others have done, because of the clinical impact of non-adherence for this patient group [3, 30, 47]. The proportion of days adherent over the 35–215 day period (T1-T2) will be calculated. To assess whether the intervention has a sustained effect we collect EM data over the period T2-T3 (180 days). Similarly, to explore changes over time we will assess the 95% adherence rate per month as well as for the total period.

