#### Primary study parameter

The primary outcome, the proportion of participants that is adherent more than 95% of the 180 days (T1-T2) in both randomization groups as measured by EM, will be analyzed with a chi-test with continuity correction. The cut-off score of 95% is in accordance with the criteria of the Basel Assessment of Adherence to Immunosuppressive Medications Scale: BAASIS interview [48].

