#### Secondary study parameters

The proportions of adherent participants based on the CAS in both randomization groups will be analyzed with a chi-test with continuity correction. The influence of biological markers on adherence will be analyzed with a logistic regression.

The continuous secondary outcomes will be analyzed with linear multi-level regression analyses. The patients form the upper level, their measures at T1 and T2 the lower level. The covariance structure will be determined with the deviance score applying restricted maximum likelihood. Treatment group, T2, the group-T2 interaction and age will be postulated as fixed effects. In case of an abnormal distribution of the scores, an appropriate transformation (logarithmic, polynomial or Blom [73]) will be applied. If no satisfying transformation can be found, the outcome will be dichotomized on the median, and a multilevel logistic regression analysis will be performed. Binary outcomes will be analyzed with multilevel logistic regression analysis, using the same levels and fixed effects as described for linear multi-level regression analysis.

To analyze whether the intervention is sustainable 6 months after the treatment, a logistic multilevel analysis will be applied including the T1, T2 and T3 measures. Adherence will be the dependent variable, and treatment group, T2, T3 and group-time interactions will be the fixed effects. The group-T2 interaction effect will present the differential intervention effect, and the T2-T3-group contrast is the effect of interest for sustainability.

To answer the question when the intervention influences the adherence most, a multi-level logistic regression analysis will be applied. The EM devices can be read every 30 days, resulting in a baseline and 6 repeated measures (at 65, 95, 125, 155, 185 and 215 days). The fixed part of the model will include treatment group, the six follow-up time points and interactions.

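### The sustainability model treats a 28-42 day run-in status and two 180-day statuses as one repeated binary response, so T1 is a different measure and the group-T2 effect is estimated inefficiently

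*Protocol article*

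**What the plan says.** All of this is in the protocol article.

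- **The rule** (Primary outcome measure): "Medication adherence is operationalized as being adherent ≥95% as registered by the EM". The Primary study parameter section words it as "adherent more than 95% of the 180 days (T1-T2"). No other rule for electronic monitoring (EM) is given.
- **The windows.** For T1, "a run-in period of 35 days (+/− 7 days) is incorporated" (Procedure). For T2, "The proportion of days adherent over the 35–215 day period (T1-T2) will be calculated" (Primary outcome measure). The same section gives 180 days for T2-T3.
- **The sustainability model** (Secondary study parameters): "a logistic multilevel analysis will be applied including the T1, T2 and T3 measures". Adherence is the dependent variable; group, T2, T3 and the group-time interactions are fixed effects. T1 is therefore the reference time. The group-T2 interaction is named as the differential intervention effect, and the group contrast between T2 and T3 as the test of sustainability.
- **The monthly model.** The outcome section announces that "to explore changes over time we will assess the 95% adherence rate per month as well as for the total period". The analysis section describes a separate model with readings every 30 days, "resulting in a baseline and 6 repeated measures (at 65, 95, 125, 155, 185 and 215 days").
- **Why there is a run-in** (Procedure): evidence that "adherence will be statistically higher when patients start to use the electronic monitoring device".

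Randomisation follows the run-in, so T1 data are pre-treatment.

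**The concern.** A percentage cut-off applied to a count of whole days is a different test in windows of different length. A short window tolerates one miss and classifies patients with much noise; a 180-day window tolerates nine and classifies them sharply. If both enter a model as the same yes/no response, a patient whose behaviour never changes can be scored as changing between T1 and T2.

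Two things are at stake. First, reported T1 and T2 percentages adherent within an arm, and monthly against 180-day percentages, would look comparable when they are not. Second, the group-T2 interaction subtracts the T1 group difference. Because T1 precedes randomisation, that difference is zero in expectation, so subtracting a coarse binary version of it mainly adds noise.

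**Working it through.** **1. The plan's own figure.** No power is stated for the secondary models. The number per arm comes from the power calculation: 95.1% vs 79.1%, two-sided alpha 0.029, power 0.80, 10% drop-out, 81 per arm. With the arcsine effect size h = 2·asin(√0.951) − 2·asin(√0.791) = 0.503, n = 2·[(2.183 + 0.842)/0.503]² = 72.3, so 73 per arm; 73/0.9 = 81.1, in line with the stated 81. The simulations below use 73 evaluable patients per arm.

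**2. Missed days allowed.** The smallest passing count is k = ceil(0.95·n); misses allowed = n − k.

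| Window (days) | Days needed | Misses allowed | Effective cut-off |
|---|---|---|---|
| 28 | 27 | 1 | 96.4% |
| 30 (month) | 29 | 1 | 96.7% |
| 35 | 34 | 1 | 97.1% |
| 39 | 38 | 1 | 97.4% |
| 40 | 38 | 2 | 95.0% |
| 42 | 40 | 2 | 95.2% |
| 180 | 171 | 9 | 95.0% |

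Under the alternative wording (more than 95%), 180 days allows 8 misses, and 40 days allows 1, since 38/40 is exactly 95%. The other rows do not change.

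**3. Chance that an unchanged patient is classed adherent.** With constant daily probability p and independent days (assumptions), P = Σ over j ≥ k of C(n,j)·p^j·(1−p)^(n−j). Example, n = 35 and p = 0.97: 0.97^35 + 35·0.03·0.97^34 = 0.344 + 0.373 = 0.717.

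| True p | 30 d | 35 d | 180 d |
|---|---|---|---|
| 0.90 | 0.18 | 0.12 | 0.01 |
| 0.95 | 0.55 | 0.47 | 0.59 |
| 0.97 | 0.77 | 0.72 | 0.95 |

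At p = 0.95, moving the T1 visit from day 39 to day 40, both inside the permitted range, changes the T1 probability from 0.41 to 0.68.

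**4. Effect on within-arm percentages.** In two simulated scenarios the control-arm share classed adherent rose from 0.48 at T1 to 0.54 at T2, and from 0.65 to 0.73, with no true change.

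**5. Power for the group effect at T2.** Random-intercept logistic model, 73 per arm, test at 0.05. Planned: T1, T2 and T3 as responses. Alternative: T2 and T3 as responses, run-in proportion of adherent days as covariate. Scenarios are assumed and defined by patient mean logit, patient SD, within-period SD and T2 effect on the logit.

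| Scenario | Runs | Planned | Alternative |
|---|---|---|---|
| A: 2.6, 1.3, 0.5, effect 0.6 | 788 | 0.59 | 0.79 |
| A, repeated | 150 | 0.49 | 0.69 |
| A, repeated | 300 | 0.56 | 0.73 |
| B: 3.0, 1.0, 0.5, effect 0.7 | 150 | 0.75 | 0.89 |
| C: 3.5, 0.8, 0.5, effect 1.0 | 150 | 0.95 | 1.00 |
| Further set, three scenarios | 200 each | 0.62; 0.62; 0.75 | 0.74; 0.85; 0.90 |

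Monte Carlo error is about 2 points at 788 runs and up to 4 at 150. Type I error, planned vs alternative, was 0.043 vs 0.043 (163 runs), 0.07 vs 0.03 (150) and 0.07 vs 0.07 (200).

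**6. Where the gain comes from** (scenario A, 300 runs):
- planned: 0.56
- same model with a hypothetical 180-day T1: 0.62
- binary T1 kept but moved to a covariate: 0.68
- run-in proportion as covariate: 0.73

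Equalising the window recovers 6 of the 17 points. Changing only the T1 window in scenarios B and C gave 0.74 to 0.79 and 0.90 to 0.92 (250 runs).

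**7. The T2-T3-by-group contrast.** Planned vs alternative: 0.51 vs 0.59 and 0.65 vs 0.68 (150 runs), 0.61 vs 0.69 and 0.55 vs 0.62 (200), 0.57 vs 0.64 (300, scenario A with no T3 effect). Changing only the T1 window: 0.47 vs 0.51 and 0.58 vs 0.62 (250). Shortening every window to 35 days would cost power: 0.26 and 0.45.

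**The case against.** The strongest reply has five parts.

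- **The sustainability test is unaffected.** A reader might infer that unequal windows weaken the test of persistence. The document does not support that: the contrast it names compares T2 with T3, both 180 days. The gains there are only 3 to 8 points, mostly within simulation error. This stands.
- **The power gain is not mainly about windows.** It comes largely from adjusting for baseline instead of modelling change, and from not dichotomising the baseline. This stands too. The gain is real and free, but should not be credited to window length.
- **No bias.** A reader might infer that T1 misclassification, or the early rise in adherence under monitoring, distorts the treatment comparison. Both arms share the same windows, T1 precedes randomisation, and the time main effects absorb a common shift. The primary chi-square test uses T1-T2 only. This stands.
- **Monthly status is never pooled with 180-day status.** Correct: it has its own model with six equal windows, and only its baseline differs in length. What remains is a caution about reporting the two rates as one criterion.
- **T1 status is not spelled out.** It could be derived from part of the run-in, and such detail may sit in an analysis plan not shown. The miss counts for T1 therefore rest on an assumption. Using T1 as a response, and as reference for the group-T2 effect, is nevertheless fixed in the article.

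**Conclusion.** The point holds as an efficiency and interpretation issue in secondary analyses. T1 status is a coarser and different measure from T2 and T3 status: one or two misses allowed against nine, and 0.72 against 0.95 probability of being classed adherent for an unchanged patient at 97% of days. T1-to-T2 changes in percent adherent within an arm therefore partly reflect window length, 6 to 8 points in the simulated control arms.

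The group-T2 interaction uses less information than the trial collects. Power was roughly 0.5-0.75 as planned and 0.7-0.9 with the run-in covariate; in scenario C, where planned power was already 0.95, there was little left to gain. About a third of the decomposed gain (6 of 17 points) came from window length, the rest from covariate adjustment on an undichotomised baseline.

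The documents do not support a claim of between-arm bias, of harm to the primary test, or of material loss in the T2-T3-by-group contrast. The conclusion assumes that adherence in this model means EM status, that T1 status is the 95% rule over the whole run-in, that days are independent at a constant rate (for the binomial table), and that the simulated scenarios are reasonable. The document gives no figures to calibrate those scenarios.

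**What to change.** 1. **Sustainability model:** keep T2 and T3 (180 days each) as the responses, take T1 out of the dependent variable, and enter each patient's run-in proportion of adherent days as a baseline covariate. Report the group effect at T2 and the T2-T3-by-group contrast. As a covariate, the run-in value need only predict later adherence; it need not be on the same scale.
2. **Monthly model:** use the six 30-day windows as responses with the same covariate.
3. **Reporting:** state the monthly cut as 29 or more of 30 days. Do not set T1, monthly and 180-day rates side by side as one criterion.
4. **While editing:** use one form of the cut-off, at least or more than 95%, since it moves the 180-day allowance between 9 and 8 misses.

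The cost is the rewording of two secondary analyses. The run-in EM data are already collected and the article reports data collection as ongoing, so the change can be dated before outcomes are compared by arm. The small downside is that the model no longer yields a T1-to-T2 change in percent adherent.

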**Secondary objectives patient**					
To test the effectiveness of the MARS-intervention in promoting the medication adherence as measured by secondary outcome measures in comparison to CAU (control group). To test whether the effectiveness of the MARS-intervention on medication adherence sustains after six months (T2-T3). To asses when the MARS-intervention influences medication adherence the most.	**Questionnaires patient**				
	Medication adherence (BAASIS)	X	X	X	X

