### Statistical analysis

#### Power calculation

To our knowledge there was no (multi) systemic intervention study carried out among kidney transplant recipients at the time this project commenced, making it difficult to conduct a power analysis based on a comparable study. Therefore, the power calculation is based upon a behavioral intervention study among a group of heart, liver and lung transplanted patients [72]. The intervention group showed an adherence proportion of 95.1% and the control group a proportion of 79.1%. As the MARS-intervention is more intensive than the intervention of Dobbels et al. [72] we will perform an interim analysis when half of the participants have been included. We applied a 2-sided alpha of 0.029 and a power of 0.80. Anticipating a drop-out of 10%, this led to a target of 81 participants in both groups, a total of 162.

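### The contrast named for sustainability measures change in the group effect from T2 to T3, so it cannot by itself show a sustained benefit, and it has low power to detect partial loss

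*Protocol article*

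**What the plan says.** Table 1 lists a secondary objective: "To test whether the effectiveness of the MARS-intervention on medication adherence sustains after six months (T2-T3"). Under Primary outcome measure, the electronic monitoring data for the second half-year are given the same purpose: "To assess whether the intervention has a sustained effect we collect EM data over the period T2-T3 (180 days").

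Under Secondary study parameters, "a logistic multilevel analysis will be applied including the T1, T2 and T3 measures". Adherence is the dependent variable, and "treatment group, T2, T3 and group-time interactions will be the fixed effects". The article then gives two terms a role. For the end of treatment, "The group-T2 interaction effect will present the differential intervention effect". For durability, "the T2-T3-group contrast is the effect of interest for sustainability". The group-T3 interaction, which compares the arms at T3 relative to T1, is in the model but is not assigned to any question.

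The article states no retention margin, does not make sustainability conditional on a T2 effect, and gives no power figure for the contrast. It also states no rule for turning the contrast into a conclusion.

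**The concern.** The contrast is the group effect at T3 minus the group effect at T2. Its null hypothesis is that the group effect did not change. That null is true when a benefit persists in full and equally true when there was no benefit at either time. A significant result can show that an effect shrank or grew, but a non-significant one cannot show that it lasted.

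The objective asks whether effectiveness sustains, so a reader of the results will look for a positive answer, and the named effect of interest cannot supply one. If the contrast is also imprecise, a trial that has lost much of its benefit by T3 will often produce a contrast that looks reassuring. A claim of durable benefit for a six-month home-based intervention could then rest on absence of evidence.

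**Working it through.** **Inputs from the protocol article (Power calculation).** Planning rates are 95.1% and 79.1%, a difference of 16.0 points. The target is 81 per group with 10% drop-out, and "We applied a 2-sided alpha of 0.029 and a power of 0.80".

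**The plan's own figure.** The arcsine formula n = 2(z₁₋α/₂ + z₁₋β)²/h², with h = 2·arcsin√0.951 − 2·arcsin√0.791 = 0.503, gives 2 × (2.183 + 0.842)²/0.503² ≈ 72.3 per arm. Then 72.3/0.9 = 80.3, i.e. 81, so the stated target is reproduced. The evaluable number is 81 × 0.9 = 72.9, i.e. 73 per arm. This sizing is for the primary outcome only.

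**Assumptions not in the documents.** Two-sided alpha is 0.05 for this secondary contrast. The within-patient correlation ρ between adherence at T2 and at T3 is 0.4 to 0.7. The control rate is constant. As a lower-rate scenario, 56% vs 40% is used.

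**Formula (risk-difference approximation to the planned logistic model).** Per arm, the variance of within-patient change is V = p₂q₂ + p₃q₃ − 2ρ√(p₂q₂·p₃q₃). SE = √[(V_MARS + V_control)/73]. Power ≈ Φ(loss/SE − 1.96), plus a negligible opposite tail.

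**Cap on ρ.** Two binary variables with different rates cannot be perfectly correlated. With rates p_low and p_high, the maximum is √[p_low(1 − p_high)/(p_high(1 − p_low))].
- 95.1% falling to 87.1%: √[(0.871 × 0.049)/(0.951 × 0.129)] = 0.59.
- 95.1% falling to 79.1%: √[(0.791 × 0.049)/(0.951 × 0.209)] = 0.44.

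The MARS arm uses the lower of ρ and this cap.

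**Worked case: half the effect lost, ρ = 0.4.** p₂q₂ = 0.951 × 0.049 = 0.0466 and p₃q₃ = 0.871 × 0.129 = 0.1124, so V_MARS = 0.1590 − 0.8 × 0.0724 = 0.1011. V_control = 2 × 0.1653 × 0.6 = 0.1984. SE = √(0.2995/73) = 0.0640. Power = Φ(0.08/0.0640 − 1.96) = Φ(−0.71) = 0.24.

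| Scenario | SE, ρ = 0.4 | Power | SE, ρ = 0.7 (capped) | Power |
|---|---|---|---|---|
| Planning rates, 8 of 16 points lost | 0.064 | 0.24 | 0.049 | 0.38 |
| Planning rates, all 16 lost | 0.068 | 0.65 | 0.057 | 0.81 |
| 56% vs 40%, 8 of 16 lost | 0.090 | 0.15 | 0.063 | 0.24 |
| 56% vs 40%, all 16 lost | 0.089 | 0.43 | 0.063 | 0.72 |

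In both half-loss rows the 95% CI half-width (1.96 × SE) exceeds the 8-point loss: about 10 to 13 points at the planning rates and 12 to 18 at the lower ones.

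**Cross-check on the log-odds scale.** This was a simulation of 200,000 trials per scenario, with 73 per arm, planning rates, a Wald test of the contrast, and correlations 0 / 0.3 / 0.5 / 0.7 capped as above. It is a marginal approximation to the multilevel model.

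| True state | Contrast non-significant |
|---|---|
| No effect at any time | 95 / 95 / 95 / 96% |
| Effect fully kept | 97 to 99% |
| Half the risk difference lost | 76 / 68 / 59 / 48% |
| Half the log-odds ratio lost | 86 / 82 / 78 / 71% |
| Effect wholly lost | 40 / 24 / 13 / 7% |

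The first two rows show the structural point: the contrast hardly separates a kept effect from no effect.

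If a significant T2 effect favouring MARS is also required, a no-effect trial passes both steps in only about 1 to 2% of cases. Half-loss trials that meet this requirement still show a non-significant contrast in 44 to 71% (risk difference) or 68 to 83% (log-odds ratio).

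The simple group difference at T3, tested at 0.05, has power of about 83% if the effect is fully kept. Power is 23% if half the risk difference remains and 39% if half the log-odds ratio remains. It is significant in favour of MARS in about 2% of trials with no effect.

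**The case against.** The strongest reply is that the plan names an effect of interest and not a decision rule. An effect of interest can be reported as an estimate with a confidence interval, and the rules for interpreting it may sit in an analysis plan that is not shown. This stands. A reader might infer that, under the plan, an ineffective intervention would pass as sustained in about 95% of trials. The documents do not support that. They nowhere equate non-significance with sustainment, and the same sentence presents the group-T2 effect. With no effect at T2 there is nothing to sustain, and reading the two terms together brings the figure down to about 1 to 2%. The article does not write that condition down, but a competent reader would apply it.

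A second reply is that whether effectiveness sustains from T2 to T3 is a question about change, which the contrast addresses directly. This stands in part. The contrast is a legitimate estimate of decay and should be kept. As a test, however, it can supply evidence only against sustainment.

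A third reply is that a real relapse would be caught. At the planning rates this is largely true of complete loss, where power is 0.65 to 0.81, and higher in the log-odds simulation at correlations of 0.3 and above. A general statement that relapse is likely to be missed would therefore go too far. It holds for partial loss, or at lower adherence rates that the documents do not give. Even for partial loss there is an exception: with half the risk difference lost and the highest correlation, the log-odds simulation misses it about half the time (48%).

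Finally, the T3 effect has its own limits. It has low power if only half the effect remains, and a positive result does not show full retention. Its failure is the safer one, though, because a non-significant T3 effect yields no claim of benefit.

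**Conclusion.** The point holds in this form: the contrast assigned to sustainability has no change as its null, so it cannot provide positive evidence of a sustained benefit, and no other term or margin is assigned to that objective. The practical exposure is partial loss. Half of the 16-point effect could disappear and the contrast would detect it with power of about 0.24 to 0.38 at the planning rates, or 0.15 to 0.24 at 56% vs 40%. Complete loss is detected with about 0.65 to 0.81, or 0.43 to 0.72 at the lower rates.

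These figures rest on 73 evaluable per arm, two-sided alpha 0.05, an assumed correlation of 0.4 to 0.7 and a risk-difference approximation. On the log-odds scale, power for half the risk difference lost is somewhat higher (24 to 52% over correlations 0 to 0.7), and for half the log-odds ratio lost it is lower (14 to 29%). Further attrition by T3, or a smaller sample after the halt in inclusion described under Procedure, would lower power.

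The matter concerns one secondary objective and leaves the primary analysis untouched. It should be corrected, but it does not threaten the trial.

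**What to change.** In Secondary study parameters, replace the sentence that assigns the contrast with three statements:

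1. The estimate of sustained benefit is the group effect at T3 relative to T1 (the group-T3 term already in the model), reported with a risk difference and 95% CI. Sustained benefit is claimed only if an intervention effect was shown at T2 and the T3 effect favours MARS.
2. The T2-T3-group contrast is reported with its 95% CI as the estimate of decay.
3. No conclusion of maintenance is drawn from a non-significant contrast.

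The cost is a few sentences; the model and the data stay the same, and the article says data collection is still ongoing. The downside is low power at T3 if only half the effect remains, about 23 to 39%. That figure is for the simple group difference at T3; precision relative to T1 will also depend on the T1-T3 correlation, which the documents do not give. A positive T3 result should be described as benefit still present, not as full retention, which is why the decay estimate and its interval belong beside it.
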